**5.d Study populations and evaluations**

**5.d.1 UW Primary Infection Clinic (PIC) Cohort study**

As described in **4. Preliminary Studies**, 319 subjects with acute and early HIV-1 infection have been enrolled in an observational, natural history study through the PIC. When available, we will use stored samples from subjects who were enrolled in the PIC Cohort study after 1996 and who otherwise meet criteria for one of the studies described in **5.c Study design and data analysis**. Subjects previously enrolled into the cohort who meet these criteria and who remain in active follow-up will continue to be followed.

In order to be eligible for ongoing enrollment in the PIC, individuals must be at least 16 years old and have acute or very early HIV-1 infection, defined as one of the following:

 plasma HIV-1 RNA greater than 2000 copies/mL with a negative HIV-1 enzyme immunoassay (EIA) or negative/indeterminate Western blot

 positive EIA with a documented negative HIV-1 antibody test within the last four months, a credible history of exposure, symptoms consistent with the acute retroviral syndrome [164], and a plasma HIV-1 RNA greater than 400,000 copies/mL.

Results of rapid HIV-1 antibody testing will not be sufficient to document acute HIV-1 infection, because we have identified several persons who tested HIV-negative by a rapid HIV-1 antibody test but who were HIV-positive by both a 1st or 2nd generation EIA and Western Blot confirmatory assays (Fiebig stage V *and VI*) [44]. Subjects must be screened for enrollment in the cohort within 30 days of the estimated date of HIV-1 infection, defined as the onset date of symptoms consistent with the acute retroviral syndrome or, for asymptomatic subjects, the midpoint between the last negative and first positive HIV-1 tests.

The schedule of evaluations (**Table 11**) for newly-enrolled subjects will be similar to the schedule of evaluations that has previously been employed for all subjects enrolled in the PIC cohort with the removal of the study visit (V10) 32 weeks after study enrollment to minimize blood volume and to reduce costs. Study visits will occur at more frequent intervals than required as a part of this application in order to have specimens available for more detailed analyses related to this and other projects in the future.

**Table 11: PIC Cohort study (The virologic and immunologic events in acute/early HIV-1 infection): schedule of e**valuations

| Visit # | V1  Screen | V2  Entry | V3  Wk 1 | V4  Wk 2 | V 4.5  Wk3 | V5  Wk 4 | V6  Wk 8 | V7  Wk 12 | V8  Wk 16 | V9  Wk 24 | V11  Wk 48 | Every 6  Months |
| --- | --- | --- | --- | --- | --- | --- | --- | --- | --- | --- | --- | --- |
| Clinic Visit | X | X | X | X | X | X | X | X | X | X | X | X |
| Informed Consent | X | X |  |  |  |  |  |  |  |  |  |  |
| H&P |  | X |  |  |  |  |  |  | X |  | X | X |
| HIV-1 antibody | X | X |  | X1 |  | X1 | X1 |  | X1 | X1 |  |  |
| HIV-1 RNA testing | X | X | X | X | X | X | X | X | X | X | X | X |
| CBC/T Cell Subsets | X | X |  | X |  | X | X | X | X | X | X | X |
| Genital secretions2 |  | X | X | X | X | X | X | X | X | X | X | X |
| STI screening3 |  | X |  |  |  |  |  |  |  |  |  | X |
| Blood volume (mL) | 118 | 118 | 8.5 | 64 | 8.5 | 118 | 118 | 58 | 118 | 118 | 180 | 180 |
| Length of visit (min) | 60 | 90 | 20 | 30 | 20 | 30 | 30 | 30 | 45 | 45 | 45 | 45 |

H&P: history and physical exam; CBC: complete blood count

Note: If participants initiate ARV therapy, they will restart the schedule of evaluations with a repeat Entry visit.

1After the Entry Visit, HIV-1 antibody testing to be followed only until a participant has a confirmed positive result.

2Optional procedure. Participating subjects will be asked to collect genital secretions at every study visit except for day 3.

3Subjects will be offered screening for sexually transmitted infections (STIs) at study entry and at yearly intervals. Screening could include: blood for syphilis and HSV serologies, pharyngeal swab for gonorrhea culture, urine for NAAT for gonorrhea and chlamydia, and rectal swab for culture for gonorrhea and chlamydia. These will be transported by courier to the PHSKC laboratory.

At the initial visit, after obtaining informed consent, subjects will be asked questions about their medical history and about risk factors for HIV-1 acquisition, sex partners, and injection drug use. Subjects will be screened for HIV-1 infection, including HIV-1 antibody and HIV-1 RNA testing, and blood will be stored for future testing. At the Entry visit, if the subject is eligible for enrollment, s/he will be asked to refer potential source partners for enrollment into the PIC Partners study. A physical examination will be performed, including documentation of circumcision status. Blood will be drawn at this visit and at subsequent visits for clinical tests (i.e. CD4+ T-cell count and HIV-1 RNA level) as indicated in the schedule of evaluations. Blood, semen, and other specimens that are not utilized for the projects detailed in this application will be available for immunologic and virologic investigations to be funded by other project and program grant applications that are currently in process. If subjects initiate ARV therapy during the study, they will restart the schedule of evaluations, beginning with the Entry visit (V2). During follow-up, subjects will be asked questions about continued risk behaviors, ARV treatment and adherence, other concomitant medications, signs/symptoms, and diagnoses.

Men will be instructed not to ejaculate for 48 hours prior to collection of semen specimens, to ejaculate directly into the sterile specimen container, and to use no lubricant except for water. If collected at home, the subject will bring the specimen to the PIC within one hour after collection. Whether collected in the PIC or brought to the PIC after collection, the specimen will be sent immediately to the UW Clinical Retrovirology Laboratory.

**5.d.2 PIC Partners study**

As part of the UW PIC Cohort and PIC Partners studies (described in **4. Preliminary Studies**), we have, to date, previously identified a total of *36* partner-pairs and have confirmed *19* transmissions; confirmation of remaining 17 unconfirmed partner-pairs is pending. PIC Partners continue to be recruited and enrolled through referrals from subjects with primary HIV-1 infection enrolled into the UW PIC Cohort study (**Figure 6**).

**Figure 6: Methods for recruitment and identification of transmitting (source) partners for PIC Partners study**

PIC enrollee presents with primary HIV-1 infection, is eligible, and consents to PIC Cohort study.

PIC enrollee identifies all partners with whom s/he had contact in the 3 months prior to the estimated date of HIV-1 acquisition.

Potential source partner is notified by PIC enrollee or by PIC staff and consents to PIC Partners study.

PIC Partner is found to be infected with HIV-1, and viral sequences of PIC enrollee and Partner show high degree of homology.

When available, we will use stored samples for Aim #3 from subjects who previously enrolled in the PIC Partners study. We will also continue to identify putative source partners of new subjects enrolled into the PIC Cohort study. Persons will be eligible for screening if they are at least 18 years old and were identified by the PIC enrollee to be a sex partner or needle-sharing partner in the three months prior to the PIC enrollee's estimated date of HIV-1 acquisition. Enrollees can refer partners or have referral orchestrated by PIC clinicians. If referral is performed by PIC staff, partner notification follows procedures outlined in the Washington State HIV Partner Notification Guide, and the identity of the PIC enrollee is not revealed to the potential source partner. Contact with all eligible partners of PIC enrollees will be attempted, and the schedule of evaluations (**Table 12**) will be similar to the current PIC Partners schedule of evaluations. Blood and other specimens not utilized for the aims detailed in this application will be stored to be available for future immunologic and virologic investigations.

**Table 12: PIC Partners study schedule o**f evaluations

|  | Visit #1  Screening | Visit #2  Entry |
| --- | --- | --- |
| Informed Consent | X |  |
| Screening Questionnaire | X |  |
| HIV-1 testing (antibody, LS-EIA, Western blot, & plasma HIV-1 RNA) | X |  |
| Vital signs/weight |  | X |
| History and Physical Exam |  | X |
| CD4+ T-cell count/subsets |  | X |
| Immunology panel (HLA typing, CTL assays) |  | X1 |
| Serum storage |  | X1 |
| Plasma/PBMCs storage |  | X1 |
| Genital secretions |  | X2,3 |
| *STI screening4* |  | *X* |
| Blood volume (mL) | 15.5 | 111 |
| Length of visit (min) | 60 | 60 |

1Specimens will be collected and stored for future testing. More detailed laboratory studies will only be performed if sequence analysis confirms that transmission occurred from the PIC Partner to the PIC enrollee.

2Collection of semen specimens is recommended but optional.

3An additional 17mL of blood will be collected during a 20 minute visit if the collection of semen specimens is >4 days after Visit #2.

*4Subjects will be offered screening for sexually transmitted infections (STIs) at study entry, including blood for syphilis and HSV serologies, pharyngeal swab for gonorrhea culture, urine for NAAT for gonorrhea and chlamydia, and rectal swab for culture for gonorrhea and chlamydia. These will be transported by courier to the PHSKC laboratory.*

At the initial visit, partners not known to be HIV-positive will be informed of their exposure, asked about symptoms consistent with acute or established HIV-1 infection, and screened for HIV-1 infection. Partners will complete a behavioral questionnaire to ascertain their knowledge of their HIV-1 status and to quantify sexual and needle-sharing exposures to the PIC enrollee. If the partner is found to meet the above criteria for acute or early HIV-1 infection, s/he will be screened for additional studies available through the PIC.

Only HIV-positive partners will complete the additional evaluations and specimen collections listed in **Table 12** as Visit #2 (Entry). This visit may be combined with Visit #1 (Screening) for partners previously known to be HIV-positive. HIV-positive partners will be asked detailed information about their past medical history, including dates of prior HIV-1 testing (to estimate the date of HIV-1 infection), ARV history and previous opportunistic conditions. A physical examination will be performed, including documentation of circumcision status. Blood will be drawn for a CD4+ T-cell count and storage of serum, plasma, and PBMCs. Viral sequencing will be done in the [name] laboratory to confirm the transmission relationship between partners. Collection of genital secretions will be recommended but optional for both male and female source partners. There is no longitudinal follow-up; we anticipate that all partners should complete the evaluations within a few weeks.

Collection of semen specimens for the PIC Partners Study will be performed as described under **5.d.1 UW Primary Infection Cohort**, above. Blood will be drawn for plasma and PBMCs if semen is collected more than four days after Visit #2 (Entry). For women, the methods for collection and processing are as described by Reichelderfer et al [194]. After removing visible blood or clots with a swab, endocervical canal fluid is collected using three filter paper strips (TearFloTM). Each strip is placed into the cervical os, and cervical canal fluid is absorbed past the 10mm mark on each strip (15μL). Strips are removed, cut at the 10mm mark, and placed into vials containing 225 μL of guanidinium solution. Genital secretions are collected by cervical-vaginal lavage (CVL) using 10ml of sterile non-bacteriostatic saline, and endocervical canal cells are collected by cytobrush. The CVL fluid is put on ice and sent immediately to the UW Clinical Retrovirology laboratory.

**5.e Laboratory methods**

**5.e.1 Routine laboratory testing**

Routine tests including complete blood counts, lymphocyte subsets, HIV-1 EIA and Western Blot assays will be done by the UW Department of Laboratory Medicine Laboratory using standard techniques. Lymphocyte subsets will be determined using flow cytometry in a lab certified by the NIAID’s Immunology Quality Assurance Program. The SeaPIP Virology Core Laboratory will continue to separate plasma and cells and serve as the central storage facility for the specimens collected for this protocol.

**5.e.2 HIV-1 RNA quantification in blood plasma and genital secretions**

Blood plasma HIV-1 RNA quantification is performed by an independently-validated real-time RT-PCR amplification assay with lower limits of detection equal to 50 copies/mL [195]. Results of specimens collected between 1996 and 2002 were initially tested with branched DNA (bDNA) assays with lower limits of detection of 50 and 500 copies/mL (Chiron Corporation, Emeryville, CA). When specimens were available, results censored at 500 copies/mL have been re-tested using an ultra-sensitive reverse transcription polymerase chain reaction (RT-PCR) assay (Roche, Branchburg, NJ) or the real-time RT-PCR assay. Since 2002, all specimens have been evaluated by an RT-PCR assay.

Semen is processed within two hours of collection [196]. Specimens are diluted to reduce viscosity and centrifuged to separate the seminal plasma and cell pellet. Boom (silica) extraction is performed to minimize effect of inhibitory factors, and HIV-1 RNA is quantified using the real-time RT-PCR assay (lower limit of detection equal to 300 copies/mL) or Roche Amplicor HIV-1-1 Monitor versions 1.0 or 1.5 (lower limit of detection equal to 200 copies/mL) [197]. For both blood and semen, specimens with HIV-1 RNA levels below the lower limits of detection will be assigned censored values.

For women, CVL fluid is transported on ice and centrifuged after arrival at the laboratory, and the supernatant is frozen at –80oC. The cytobrush is put into PBS and agitated, the cells are separated by centrifugation, and the cell pellet is stored at –80oC. These specimens will be used for RNA quantitation and OLA.

**5.e.3** RT-PCR and PCR for genotyping of HIV-1 *pol*

RNA is extracted from 0.2 ml of plasma, as previously described [145]. DNA is extracted from PBMC using the Puregene Cell and Tissue kit (Gentra Systems, Inc., Minneapolis, MN) according to manufacturers' instructions. Ten μl of RNA extracted from plasma is reverse transcribed using the GeneAmp RNA PCR Core kit (Applied Biosystems, Foster City, Calif.). The first-round PCR of cDNA or of DNA extracted from PBMC is carried out in a 50-μl reaction mixture containing 10 μl of cDNA or 1 μg DNA, 1× PCR buffer, 1.5 mM MgCl2, 0.2 mM deoxynucleoside triphosphates, 20 pmol of the primers PRA and RTA [145], and 2.5 U of Taq DNA polymerase (Sigma-Aldrich Corp., St. Louis, Mo.). Cycling conditions as described previously [145] with a final extension at 72°C for 7 min. Second-round PCR contains 2 μl of first-round product and 20 pmol of primers PRB and RT3 [145]. The amplicon, a 1,193-bp DNA fragment extending from nucleotide 1of HIV-1-pro to nucleotide 711 of the RT gene according to the HXB-2 numbering system, is visualized in a 1% agarose gel with ethidium bromide staining. The amount of DNA resulting from nested PCR is estimated based on the band intensity relative to a DNA Mass Ladder on the same gel. Further testing is performed on samples having DNA concentrations between12 to 20 ng/μl.

**5.e.4 Consensus sequencing**

The PCR amplicon is purified by treatment with ExoSAP-IT (Amersham Biosciences, Piscataway, N.J.). Four primers are used in bidirectional sequencing of the PCR products, including protease primers PRB and PR2 and RT primers RT4 and RT3. PCR amplicon is added to a sequencing reaction using fluorescence-labeled dideoxynucleotide chain terminators (AB PRISM Big Dye Terminator Cycle Sequencing Ready Reaction kit, version 1.1; Applied Biosystems). Cycling conditions were 96°C for 30 s, 50°C for 15 s, and 60°C for 4 min for 25 cycles. Samples are submitted to a core sequencing facility where excess dye terminators are removed and samples are submitted to a 3730XL automated sequencer (Applied Biosystems). Sequences are analyzed by Sequencher, version 3.0 (Gene Codes Corp, Ann Arbor, Mich.), with the presence of major and minor peaks recognized when visible in each of the bidirectional strands. The Stanford HIV-1seq Sequence Analysis Program [151] identified mutations within the sequences. As part of quality control procedures, assembled sequences are reviewed by a second person or at a later date to confirm results. To monitor for cross-contamination, genotypes generated are compared to all of those produced as part of this study by aligning them in ClustalX and reviewing the neighbor-joining phylogenetic tree. If a specimen more closely matches an unrelated specimen, a new aliquot is extracted and sequenced. Biannual verification is performed in the laboratory using blinded specimens provided by Rush's Virology Quality Assurance Laboratory.

**5.e.5 Oligonucleotide ligation assay (OLA)**

OLA targets specific wild-type or mutant codons for primary HIV-1 drug resistance mutations. Wild-type probes are labeled with digoxigenin *(D),* and mutant probes are labeled with fluorescein (*F*). In the following example, K103N, which confers resistance to non-nucleoside reverse transcriptase inhibitors (NNRTIs), is a mutation from the wild-type sequence AAA (lysine: K) to AAC (asparagine: N). The oligonucleotide probes, labeling, and sequence of steps used to detect this mutation by OLA are as follows:

5' 3'

common probe: **AAA**-TCA-GTA-ACA-GTA-CTG-GAT-GTG-GGT-*Biotin*

wild-type probe: *D*-AC-ATC-CCG-CAG-GGT-TAA-AAA-AAG-**AAA**

mutant probe: *F*-AC-ATC-CCG-CAG-GGT-TAA-AAA-AAG-**AAC**

The mutant or wild-type probe and common probe anneal to adjacent complementary sequences in the PCR product of the region of *pol* encoding reverse transcriptase. When the probes are perfectly complementary at the two bases on either side of the ligation site, the probes are covalently bound by DNA ligase.

*F*-AC-ATC-CCG-CAG-GGT-TAA-AAA-AAG**-AAC AAA**-TCA-GTA-ACA-GTA-CTG-GAT-GTG-GGT -*Biotin*

** **

…TG-TAG-GGC-GTC-CCA-ATT-TTT- TTC- TTG - TTT -AGT-CAT- TGT-CAT-GAC-CTA-CAC-CCA…

**Figure 7: Capture of biotinylated**

**probes on the ELISA plate [1]**

*F*-AC-ATC-CCG-CAG-GGT-TAA-AAA-AAG**-AAC - AAA**-TCA-GTA-ACA-GTA-CTG-GAT-GTG-GGT -*Biotin*

…TG-TAG-GGC-GTC-CCA-ATT-TTT- TTC- TTG - TTT -AGT-CAT- TGT-CAT-GAC-CTA-CAC-CCA…

The ligation products are then captured onto a streptavidin-coated ELISA plate (**Figure 7**), and alkaline phosphatase (AP) labeled anti-fluorescein antibodies and horseradish peroxidase (POD) labeled anti-digoxigenin antibodies are added sequentially. The AP (magenta) and POD (yellow) labeling is quantified by optical density (O.D.) using an ELISA plate reader. In the example above, only mutant virus (magenta) would be detected; however, mixtures of both wild type and mutant viruses are detectable by OLA. Indeterminate reactions occur 2-7% of the time and are typically a result of failure of the ligation reaction due to polymorphisms usually occurring at or adjacent to the two bases to either side of the ligation site. Under those circumstances, no color is produced.

**Figure 8: Examples of results of OLA testing for M184V**

**Figure 8:** Examples of optical densities (ODs) from negative controls; 2%, 5%, and 100% dilutions of cloned mutant virus; and subject samples are shown. All samples are tested in duplicate. A sample is identified as mutant (grey bar) if the mean OD for the two samples at 490nm is greater than the OD for the 5% mutant. This threshold is indicated by the horizontal line. If this requirement is met, but the OD is less than 0.2, the sample is re-tested. If the re-tested sample is again greater than the OD for the 5% mutant, a mutant variant is presumed present. 95% confidence intervals for ODs are indicated by vertical hash marks.

The mutations to be tested include K65R, K70R, L74V, M184V, T215F/Y (NRTI resistance); K103N, Y181C, and G190A (NNRTI resistance); and D30N, I50V, V82S/A/T, I84V, N88D, and L90M (PI resistance). For the semi-quantitative assays, comparisons will include 2%, 5%, 10%, 30% and 50% dilutions of known mutant virus after DNA viral quantification (**Figure 8**). For quality control purposes, duplicates of test specimens and all controls [water (negative control), mutant (positive control), and wild-type (positive control)] are run on the same plate. Biannual verification of the assay is performed using blinded specimens previously identified by consensus sequencing.

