**2. Specific Aims**

Reports of transmitted HIV-1 drug resistance are increasing worldwide. In Seattle, Washington, 11% of ARV-naïve persons have HIV-1 drug resistance detected by consensus sequencing [10], and this estimate is likely to be conservative because consensus sequencing cannot detect low-frequency viral variants [11-16]. In a pilot project at the University of Washington Primary Infection Clinic (PIC), low-frequency HIV-1 drug resistance was detected by the oligonucleotide ligation assay (OLA) in *28* (*30%) of 94* subjects with primary HIV-1 infection who had no mutations detected by consensus sequencing. *Our understanding of transmitted HIV-1 drug resistance is superficial and incomplete.* We have designed studies that will better define the clinical and public health implications of low-frequency HIV-1 drug resistance mutations. We propose the following specific aims:

**Aim #1: Determine whether the "level" of detection of HIV-1 drug resistance variants predicts the duration of detection of these variants over time since HIV-1 acquisition.**

Rationale: Studies using consensus sequencing have shown that majority variants are detected for years after HIV-1 acquisition [9, 17-25], but we could find no corresponding studies of low-frequency variants. Whether transmitted mutants continue to be detected ("persist") or are overgrown by wild-type viruses may be related to their levels at the time of HIV-1 acquisition, which may vary in PBMCs, blood, and seminal plasma [26, 27].

Methods: We will use OLA to quantify the level (<5%, 5-10%, 10-30%, 30-50%, and >50%) of mutant variants in ARV-naive subjects in the PIC cohort at baseline (the first available specimens) and 6 and 12 months after infection. Analyses will compare the detection of mutations in PBMCs compared to blood and seminal plasma and will evaluate the association between the baseline level of mutant variants and rate of continued detection.

Hypothesis: A greater proportion of untreated subjects will have mutations that remain detectable in PBMCs during follow-up compared to blood and seminal plasma, and a smaller proportion will have low-frequency mutations that remain detectable compared to subjects with mutations detected by consensus sequencing.

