Data obtained for this aim will be analyzed by logistic regression using generalized estimating equations (GEE) to account for correlated data and adjusting for the presence of mutations in PBMCs and/or plasma at baseline and the level of detection (<5%, 5-10%, 10-30%, 30-50%, or >50% of the viral quasi-species) of the mutation at baseline. We will also explore differences in the detection of mutations in seminal versus blood plasma and the detection of specific mutations (e.g. M184V) over time in PBMCs, blood and seminal plasma; however, we are unlikely to have sufficient power for these comparisons to perform definitive analyses.

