**5.c.2 Aim #2: Quantify the increase in detection of low-frequency mutations in PBMCs during ARV therapy.**

The primary objectives of the study described in this aim will evaluate changes in the detection of low-frequency mutations in PBMCs over time during ARV therapy and the virologic consequences of ARV therapy in the setting of transmitted low-frequency HIV-1 drug resistance. We hypothesize that, over time, additional mutations will be detected in a greater proportion of treated subjects with transmitted drug resistance compared to treated subjects without HIV-1 drug resistance detected at baseline, because the relative level to which viral replication is suppressed will be diminished in the former group. Secondary analyses will explore associations between specific HIV-1 drug resistance mutations, the interval between HIV-1 acquisition and the start of ARV therapy, the increased detection of HIV-1 drug resistance mutations, and treatment outcomes including time to virologic suppression and time to virologic failure.

This longitudinal study will evaluate subjects enrolled in the PIC cohort within 30 days of the estimated date of HIV-1 infection, who initiate ARV therapy at any point following the baseline evaluation, and who achieve undetectable HIV-1 RNA levels (less than 50 copies/mL) within six months after the start of ARV therapy. OLA will be performed using PBMCs collected at the visit immediately prior to the start of ARV therapy (unless this visit is within 4 weeks from the baseline specimen) and in specimens obtained 6 and 12 months following the start of treatment. The detection of a new mutation will be defined as any mutation detected during follow-up that was never previously detected. Additional analyses will use the semi-quantitative nature of OLA to evaluate the changes in levels of mutations during ARV treatment (i.e. <5%, 5-10%, 10-30%, 30-50% >50% of the viral quasi-species) and the reappearance of mutations that had been detected at baseline but were lost to detection prior to the start of ARV therapy in the absence of ARV selection pressures.

**Table 9: Sample size needed in each arm to detect a difference in proportion of subjects with new low-frequency mutations**

|  | | Percent of subjects with low-frequency mutations at baseline who have new mutations detected after start of ARVs | | | |
| --- | --- | --- | --- | --- | --- |
| 20% | 30% | 40% | 50% |

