To further explore which specific mutations are more likely to be transmitted and result in subsequent HIV-1 infection, we will conduct a logistic regression analysis with generalized estimating equations to account for correlation of the presence of different mutations within the same source partner. In this analysis, each individual mutation will be evaluated, with the outcome in the regression model; transmitted to partner Yes/No. Indicator covariates will be used to identify specific mutations. To account for the potential loss of detection of mutants over time, an exploratory analysis will adjust for the estimated time between the transmission event and the dates samples are obtained from the transmission pair for HIV-1 drug resistance testing.

We will also use the semi-quantitative nature of OLA to categorize HIV-1 drug resistance mutations as comprising <5%, 5-10%, 10-30%, 30-50%, and 50-100% of the viral quasi-species. We will compare the level of specific HIV-1 drug resistance mutations in the source and recipient partners to identify, for example, whether a mutation exists as 5-10% of the population in the source partner but 10-50% in the recipient. Analyses will control for HIV-1 RNA levels at the time of HIV-1 transmission.

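### The <5% level class has no defined place beside a call rule set at the 5% standard, and using that one line for both entry and loss biases Aim 1 primary objective 2 toward its hypothesis

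*Protocol*

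**What the plan says.** **Call rule.** Section 5.e.5 (Figure 8) identifies a sample as mutant "if the mean OD for the two samples at 490nm is greater than the OD for the 5% mutant". A weak positive gets a second look: "If this requirement is met, but the OD is less than 0.2, the sample is re-tested". No matching retest is stated for a reading just below the line.

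**Level classes.** Section 2 (Aim #1, Methods) will "quantify the level (<5%, 5-10%, 10-30%, 30-50%, and >50%) of mutant variants". The Aim 1 model in section 5.c.1 adjusts for "the level of detection (<5%, 5-10%, 10-30%, 30-50%, or >50% of the viral quasi-species) of the mutation at baseline". Section 5.c.2 uses the same classes for change during therapy. Section 5.c.3 will "categorize HIV-1 drug resistance mutations as comprising <5%, 5-10%, 10-30%, 30-50%, and 50-100% of the viral quasi-species".

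**Standards.** For the semi-quantitative assay, "comparisons will include 2%, 5%, 10%, 30% and 50% dilutions of known mutant virus". A standard below the call line is therefore already planned. Section 3.f gives OLA sensitivity as 2-5% for reverse transcriptase mutations and 5-10% for protease mutations.

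**Loss and gain.** Aim 1 primary objective 2 (section 5.b) compares low-frequency with consensus-detected mutations on whether they remain detectable at 6 and 12 months. For Aim 2, "The detection of a new mutation will be defined as any mutation detected during follow-up that was never previously detected". Neither definition includes a margin of change or a confirming test.

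**The concern.** There are two linked problems.

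The first is a definition. If a mutation counts as detected only above the 5% standard, no detected mutation can have a level below 5%. The protocol does not say whether <5% means not detected, a measured 2-5% signal, or something else. The coding of a covariate in the main Aim 1 model depends on the answer. If the class means not detected, it also overlaps the other baseline covariate in that model, which is presence of the mutation in PBMCs and/or plasma.

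The second is a bias. Subjects enter Aim 1 because a reading was above 5%, and a mutation is lost when a later reading is not. A stable variant read at 6% and then at 4% counts as lost. Only variants near the line can cross it through reading error. Low-frequency variants lie near it; consensus-detected ones, at 10-50% or more of the population, do not. Objective 2 compares these two groups and expects the low-frequency group to be lost more often, so the error pushes the estimate in the hypothesised direction.

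**Working it through.** **1. The plan's own power figures.** An exact two-sided McNemar test at 0.05, using the discordant cells as tabulated in section 5.c.1:
- 40 subjects, 45% PBMC-only versus 10% plasma-only: 84.4% (stated 84%).
- 80 subjects, 50% versus 20%: 88.9% (stated 89%).

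Both reproduce. Both concern PBMCs versus plasma.

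**2. False loss at a fixed true level.** The protocol gives no assay error. Assume a stable true level t (in %) and log-normal reading error with CV 20%, 30% or 40%.

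P(reading below 5%) = Φ((ln 5 − ln t)/s), with s = √ln(1+CV²) = 0.198, 0.294, 0.385.

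Example: t = 6, CV 20% gives Φ(−0.182/0.198) = 0.18.

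| True level | CV 20% | CV 30% | CV 40% |
|---|---|---|---|
| 6% | 0.18 | 0.27 | 0.32 |
| 7% | 0.04 | 0.13 | 0.19 |
| 8% | 0.01 | 0.05 | 0.11 |
| 10% | 0.00 | 0.01 | 0.04 |
| 20% | 0.00 | 0.00 | 0.00 |

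**3. Averaged over a group, with no biological change.** Further assumptions: true levels log-uniform over 1-100%; log10 reading error SD 0.1, 0.2 or 0.3 (CV about 23%, 49% and 78%, wider than step 2); entry if the baseline reading exceeds 5%; one follow-up reading without the retest; groups split by true level at the consensus limit, which the protocol puts at 10-50%.

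| Consensus limit | Apparent loss, low-frequency (SD 0.1 / 0.2 / 0.3) | Apparent loss, consensus-detected (maximum) |
|---|---|---|
| 10% | 19 / 35 / 45% | 2.3% |
| 20% | 9 / 19 / 28% | 0.4% |
| 30% | 7 / 15 / 22% | 0.1% |
| 50% | 6 / 11 / 17% | 0.0% |

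**4. Would this alone give a significant result?** The pilot split was 28 low-frequency to 6 consensus-detected. Scaled to 40 subjects it is 33 to 7 (28/34 × 40 = 32.9), and scaled to 80 it is 66 to 14. False rejection by Fisher's exact test over the three error SDs:
- 40 subjects: 0-2% for consensus limits of 20-50%; 0-47% for a limit of 10%.
- 80 subjects: 0-65% and 10-96%.

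**5. PBMCs versus plasma.** Start from the plan's rounded baseline split (25% PBMC only, 40% plasma only, 35% both) and apply the same retention r in both compartments. PBMC-only = 0.25r + 0.35r(1−r); plasma-only = 0.40r + 0.35r(1−r). For r = 1.0, 0.8, 0.6 this gives 25% versus 40%, 26% versus 38%, and 23% versus 32%. The excess is in plasma, opposite to that hypothesis.

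**6. What a 2% line does.** Replacing ln 5 with ln 2 in step 2 for a true 6% variant gives at most Φ(−1.099/0.385) = 0.002, against 0.18-0.32 at the 5% line.

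**The case against.** The strongest reply is that <5% is simply the bottom class of a separate semi-quantitative scale. An ordinal scale applied repeatedly, and to both members of a partner pair, needs such a class. It need not be empty: the pilot had 14 plasma-only and 8 PBMC-only subjects, and each has a sub-5% result in the other compartment. This stands in part. The text does not prove that <5% is ever treated as a positive call, and a reader who infers that goes too far. But the protocol never states the benign reading, and section 5.c.1 describes the class as a level of detection.

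Safeguards exist: duplicates, controls on the same plate, the retest of weak positives, adjustment for baseline level, and an outcome worded as continued detection. They do not remove the bias. Duplicates shrink the error but leave the shared line. The retest is one-sided and at follow-up adds to apparent loss. Level is the exposure of interest, so adjusting for it cannot separate decay from cutoff error. The limitation conceded in section 5.f.1 concerns Aim 2 only and does not mention reading error.

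A reader might also infer that Aim 1 as a whole is bound to confirm itself. The documents do not support that. Aim 1 has two primary objectives, and step 5 shows that equal error does not favour the one that drives the sample size. At 40 subjects the bias alone rarely reaches significance unless the consensus limit is near 10% and the error is large.

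The objection also limits the remedy. Counting a mutation as new in Aim 2 only if every earlier reading was at or below 2% would drop a 3% variant that rises under therapy, and the protocol's summary of aims names such selection as a target. A primary loss line at 2% would lean toward persistence. It is also unsupported for protease codons, where sections 3.f and 4.f support detection only down to about 5%; these make up 22 of the 57 calls in Table 5 (39%).

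**Conclusion.** The point holds in a limited form. The <5% class conflicts with the call rule or is left undefined, and the Aim 1 model depends on it. Using one 5% line for entry and loss biases Aim 1 primary objective 2 toward its hypothesis. With no biological change, apparent loss is about 6-45% for low-frequency mutations against 0-2.3% for consensus-detected ones.

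That range rests on assumed assay error, an assumed log-uniform spread of true levels, and the protocol's wide 10-50% consensus limit. The direction does not depend on the exact values; the size does. The main harm is a distorted estimate of how long low-frequency mutations stay detectable, more than a false significant test at 40 subjects. The PBMC-versus-plasma objective and its 84% and 89% powers are unaffected. This should be corrected, but it does not undermine the study.

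**What to change.** Keep the 5% call rule for the primary analysis and the Aim 2 definition of a new mutation as written. Then:

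- For reverse transcriptase codons, use the planned 2% standard to split <5% into two classes: at or below the 2% standard (not detected), and 2 to 5% (below the call line).
- State that the baseline level covariate for a called mutation starts at 5-10%.
- Report follow-up readings in the 2 to 5% band as a separate borderline outcome.
- Repeat the low-frequency-versus-consensus comparison as a sensitivity analysis in which a borderline reading is not counted as loss.
- In Aim 2, report how many new mutations had an earlier 2 to 5% reading.
- For protease codons, do not apply the 2% line. Report duplicate repeatability near 5% and state the limitation.

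The cost is mainly wording and data coding, since the 2% dilution is already planned. A few results become borderline, and the sensitivity analysis leans toward persistence, so it should be read beside the primary result. Pilot specimens can be included only if their graded readings were kept, which the protocol does not say.
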